## Abstract

**Background:**

Association of cognitive impairment with chronic kidney disease has been reported over the last decade. Individuals show better cognitive performance after kidney transplantation than individuals on dialysis but are more likely to be affected by cognitive impairment than age-matched comparison groups. Better knowledge of the prevalence as well as course and profile of cognitive impairment is important for the design of future studies assessing the clinical impact of cognitive impairment and developing management strategies. The goal of our study is to examine the extent of cognitive impairment before and after transplantation and to derive a distinct profile of cognitive function using standard neurocognitive tests. Furthermore, we aim to assess whether transplantation per se leads to an improvement in cognitive performance.

**Methods:**

We are conducting a prospective single-center cohort study involving 100 kidney transplant individuals. Individuals who are wait-listed to receive a kidney transplantation or have already received one will be included in this study. Individuals will undergo a battery of detailed neurocognitive tests at baseline (in part before surgery), and then 3 and 12 months afterwards. Furthermore, the enrolled patients will complete a validated German version of the Cognitive Failure Questionnaire for self-assessment (s-CFQ) as well as the Hospital Anxiety and Depression Scale -Deutsche (HADS-D), a self-report screening instrument with two scales that capture anxiety and depression. In addition, a hair sample will be taken at each measurement time point for the determination of hair cortisol levels as a parameter for the cumulative hypothalamic-pituitary-adrenocortical axis activity over the previous three months. The primary outcome measure will be (a) the effect of kidney transplantation on the cognitive performance up to 12 months after transplantation and (b) the course of cognitive performance following kidney transplantation over time.

**Discussion:**

The results of our study have potentially important implications for the prevention and treatment of cognitive impairment in kidney transplant individuals. By increasing our knowledge of the neurocognitive profile and assigning the corresponding deficits, it might be possible to create an individualized training program to positively impact cognitive deficits in kidney transplant patients.

## Introduction

Kidney transplantation is the preferred therapy for individuals with end-stage renal disease (ESRD). To date, efforts to improve cardiovascular and metabolic parameters after transplantation have been made, but the cognitive aspects of chronic kidney disease (CKD) have been relatively overlooked. Association of cognitive impairment with CKD has been reported over the last decade [1–5]. Several studies suggested a prevalence of cognitive impairment in up to 80% of individuals with CKD [1, 2, 5–9]. It has been demonstrated that individuals showed better cognitive performance after kidney transplantation than dialysis individuals [10] but these individuals are also significantly more likely to be affected by cognitive impairment or dementia than age-matched comparison groups [11–13]. Additionally, kidney transplant recipients with cognitive impairment are also affected by increased mortality [14, 15]. However, the actual prevalence of cognitive impairment in transplant recipients (from deceased and living donor) is unknown. The development of cognitive functioning and the detailed degree (i.e., which cognitive domains are particularly affected) has not yet been well studied in kidney transplant individuals. Previous studies in individuals with end-stage renal disease have shown that executive functions are particularly affected [5].

Cognitive impairments are likely to imply a high individual loss of quality of life and early restriction of self-determination and of therapy adherence, which is highly necessary for treatment. Early detection is of paramount significance so as to take preventive action, assess illness-related grief, and to avoid misunderstandings during medical care [16].

Better knowledge of the prevalence as well as of the course and profile of cognitive impairment is important for designing future studies, which will assess the clinical impact of cognitive impairment and develop management strategies. A limited number of studies have concentrated on the effects of kidney transplantation on cognitive function with divergent results [13].

The goal of our study is to examine (a) the extent of cognitive impairment, (b) the course of cognitive performance in kidney transplant individuals and (c) the profile of cognitive impairment (i.e., if a certain cognitive domain is more affected than others). Furthermore, we explore the impact and temporal course of variables with a potential influence on cognitive performance as secondary research questions. In this context, variables related to stress (subjective stress, depression, and long-term activity of the hypothalamic pituitary adrenal axis (HPA)) are of special interest to us.

## Materials and methods

### Study design and enrollment

We are conducting a prospective single-center cohort study at the University Hospital Giessen and Marburg, Giessen, Germany. It complies with the Declaration of Helsinki and has been approved by the ethics committee of the Justus Liebig University Giessen (ref 195/20). Written informed consent will be signed by the individuals and by the investigator prior to the patient´s enrollment.

Our study team consists of members of the nephrology, kidney transplantation, neurology and neuropsychology departments.

### Inclusion and exclusion criteria

Individuals who are scheduled to receive a kidney transplantation (immediate—deceased kidney donor, or within the following 2 weeks—living kidney donors) or have already received a kidney transplantation in the past will be included in this study. Due to the use of a standardized psychological assessment, individuals have to be native German speakers and at least 18 years of age. individuals under the legal supervision of a caregiver and with preexisting psychiatric disorders will be excluded from the study.

The study is divided into two parts (Table 1).

**Table 1 Tab1:** Trial schedule of enrollment and assessments

		Enrollment		Post-allocation	
Study Period, Part A					
Time point		*t*_−1_	*t*_1_	*t*_2_	*t*_3_
Enrollment					
Eligibility screen		X			
Informed consent		X			
Allocation		X			
Interventions					
Kidney transplantation			X		
Assessments					
ROCFT		X		X	X
VLMT		X		X	X
TMT-A		X		X	X
WMS-R-numbers forward		X		X	X
TMT-B		X		X	X
WMS-R-numbers backwards		X		X	X
RWT		X		X	X
Study period, Part B					
Time point	*t*_−2_		*t*_−1_	*t*_1_	*t*_2_
Enrollment					
Eligibility screen			X		
Informed consent			X		
Allocation			X		
Interventions					
Kidney transplantation	X				
Assessments					
ROCFT			X	X	X
VLMT			X	X	X
TMT-A			X	X	X
WMS-R-numbers forward			X	X	X
TMT-B			X	X	X
WMS-R-numbers backwards			X	X	X
RWT			X	X	X

Part A:

All included individuals undergo a detailed neurocognitive test battery on the day of transplantation (deceased kidney donation), or within 14 days before transplantation (living kidney donation). The neurocognitive test battery will be repeated after 3 and 12 months.

For individuals on the waiting list for deceased donor kidney transplantation we aspire to also carry out neurocognitive tests during standard visits to the hospital. Standard visits are typically several years apart and the date of transplantation is unforeseeable. Therefore, we expect not to be able to gather respective data for the majority of our participants and rather, will use it descriptively and for qualitative analyses.

Part B:

All included individuals who have already undergone transplantation and are in outpatient follow-up will undergo the same neurocognitive test battery as individuals in part A at baseline, after 3 months, and after 12 months.

### Neuropsychological assessment

A battery of standardized cognitive tests will be performed at different timepoints (Table 1). Parallel test forms will be used at follow-up to account for learning effects. The order in which the parallel test forms are presented will be counterbalanced so that each parallel test form wil be administered with the same frequency at each test time point.

#### The cognitive test battery

We first administer the Mini-Mental Status Examination (MMSE) [17] as a neurocognitive screening test, together with a test battery consisting of five tests, assessing the cognitive domains of selective attention, verbal and visual memory with short-delay and long-delay memory conditions, verbal working memory, word fluency and symbol processing. Raw scores are transformed into z-scores adjusted for age, and if available sex, as well as years of education.

The individual’s degree of impairment will be stratified using the algorithm adopted by Murray and colleagues [1] based on the Mayo criteria for mild cognitive impairment (MCI) [18] and the Diagnostic and Statistical Manual, fifth Edition, criteria for major neurocognitive impairment as approximate guidelines [19].

Individuals will be classified depending on their extent of impairment and the number of affected domains as.Unimpaired: performance better than 1.5 standard deviations (SD) below the norm sample in any test considered for the classification.Mildly impaired: mild deficits (scores 1.50 to 1.99 SD below the norm sample) in only one domain.moderately impaired: deficits in two domains or a severe deficit (2.0 SD below the norm Sample) in one domain.Severely impaired: deficits in at least two domains.

The domains of executive functions (semantic and phonemic fluency, working memory, and mental flexibility), verbal memory (immediate and delayed recall, recognition), visual memory (delayed recall), and attention (symbol processing speed) are considered in the classification.

For this purpose, we will use the following validated tests (Table 2):

**Table 2 Tab2:** The different neurocognitive tests and their affiliation to a particular cognitive domain

Cognitive domain	Test
Visual memory	ROCFT
Verbal memory	VLMT
Attention	TMT A WMS-R–numbers forward
Executive function	TMT B WMS-R–numbers backwards RWT

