### Statistical analysis

This is a within-group design with three measurement time points. We will investigate the proportion (percentage) of individuals that fulfill the above mentioned criteria at each given time point as estimates of prevalence of MCI and major neurocognitive impairment. Furthermore, we will conduct repeated-measures analysis of variance to investigate changes in cognitive performance over time, as well as the influence of different predictors. Cognitive performance of the individuals as a composite score and for each cognitive domain constitutes the dependent variables. The time of measurement and other control variables listed above represent the independent variables. A possible accumulation of the type I error is counteracted by an *α*-error correction (see below). The partial Eta-squared is calculated as the effect size, and the pairwise post-hoc comparisons are also corrected for multiple comparisons. The requirement of normal distribution is evaluated by the Kolmogorov–Smirnov test. Variance homogeneity is checked by Levene’s test. If the prerequisites for parametric statistics are not fulfilled, a distribution assumption-free covariance analysis according to the Quade model with rank-transformed variables is performed as an alternative.

Further questions are evaluated in terms of exploratory data analysis. Group differences are assessed using the t-test for independent samples or the Mann–Whitney-*U* test, depending on the scale level. Panels with discrete characteristics are analyzed with the *χ*^2^-test. Measures of correlation for discrete variables represent the contingency coefficients. For continuous characteristics, correlation measures according to Pearson (product-moment correlation) or Spearman (rank correlation) are used depending on the data level, in exceptional cases also according to Kendall (rank correlation without equidistance assumption).

The global significance level is set at *α* = 0.05. A false discovery rate (FDR) is calculated for *α*-error correction in multiple comparisons [35]. In the stepwise procedure, p-values are ranked in descending order; the null hypothesis is rejected if:1$$p(i) \le \frac{i}{m}\alpha$$ where *m* represents the number of *p* values and *i* the rank of the *p* value. Assuming *i* = 1, the FDR is equivalent to the Bonferroni correction.

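### The moderate and severe impairment classes overlap for every patient with exactly two deficient domains, so the split between them cannot be determined from the printed rule

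*Protocol article*

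**What the plan says.** The section on the cognitive test battery takes its grading from a published study: "The individual’s degree of impairment will be stratified using the algorithm adopted by" that study's authors. It gives the basis of the grading as "Individuals will be classified depending on their extent of impairment and the number of affected domains" and then prints four classes.

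- Unimpaired: "performance better than 1.5 standard deviations (SD) below the norm sample in any test considered for the classification".
- Mild: "mild deficits (scores 1.50 to 1.99 SD below the norm sample) in only one domain".
- Moderate, followed directly by severe: "deficits in two domains or a severe deficit (2.0 SD below the norm Sample) in one domain.Severely impaired: deficits in at least two domains".

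Four domains enter the classification: executive functions, verbal memory, visual memory and attention. For the last of these the text reads "attention (symbol processing speed) are considered in the classification". Table 2 lists TMT-A and WMS-R digit span forward under attention.

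The Statistical analysis section takes the proportion of patients who meet these criteria at each time point "as estimates of prevalence of MCI and major neurocognitive impairment".

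**The concern.** Two deficient domains satisfy the first branch of the moderate class. They also satisfy the severe class, which asks for two or more domains and says nothing about how deep the deficits must be. The article has no tie-break.

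The extent of impairment is goal (a) in the Introduction, and the sample size section opens with the prevalence of MCI or dementia. The boundary between moderate and severe bears on how milder and major impairment are separated. If the reading is chosen once the scores are known, the reported severe share becomes an uncontrolled analytic choice.

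**Working it through.** The article states no prevalence figure to reproduce. The check is one of logic, followed by a sizing under stated assumptions.

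**Step 1: enumerate the patterns.** Each of the four domains has no deficit, a mild deficit or a severe deficit, which gives 3^4 = 81 patterns. The printed rules are applied with unimpaired read as better than -1.5 SD in every classified test.

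| Deficient domains | Patterns | Class as printed |
|---|---|---|
| None | 1 | Unimpaired |
| One, mild | 4 | Mild |
| One, severe | 4 | Moderate |
| Exactly two | 6 pairs × 2² = 24 | Moderate and severe |
| Three or four | 4 × 2³ + 2⁴ = 48 | Severe |

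So 1 + 4 + 4 + 48 = 57 patterns fall in one class and 24 fall in two. All 24 are moderate/severe overlaps. No pattern is left out.

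**Step 2: test whether a precedence rule would rescue the text.**

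- Severe first: the two-domain branch of moderate becomes empty. Two scores of -1.5 SD in different domains then rank above a single score far below -2.0 SD, although the section says that extent counts as well as number.
- Moderate first: severe then means three or more domains, which contradicts its own threshold of two.

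Neither order leaves both printed definitions intact.

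**Step 3: size the overlap.** Assumed inputs, none of them from the article: one normal z-score per domain, equal correlation between domains, a domain deficient at or below -1.5 SD, a severe deficit at or below -2.0 SD, and 400,000 simulated patients per scenario.

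| Patient mean (SD) | Correlation | In both classes | Severe as printed (two or more domains) | Severe if two-domain cases go to moderate | Severe if two deficits at or below -2.0 SD are required |
|---|---|---|---|---|---|
| 0 | 0.3 | 3.7% | 4.7% | 0.9% | 1.0% |
| 0 | 0.6 | 3.9% | 6.4% | 2.5% | 1.8% |
| -0.5 | 0.3 | 11.0% | 15.6% | 4.6% | 4.7% |
| -0.5 | 0.6 | 8.9% | 17.2% | 8.4% | 6.4% |
| -1.0 | 0.3 | 20.9% | 36.6% | 15.7% | 15.6% |
| -1.0 | 0.6 | 14.5% | 35.7% | 21.2% | 17.3% |

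Printed rule against two-domain cases as moderate: the ratio runs from 35.7/21.2 = 1.7 to 4.7/0.9 = 5.2. Printed rule against the graded rule: from 35.7/17.3 = 2.1 to 4.7/1.0 = 4.7.

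**Step 4: vary how a domain is scored.** The article does not say whether one low score makes a whole domain deficient. A second model uses nine scores (four executive, three verbal memory, one visual, one attention), with correlations of 0.4 to 0.6 within and 0.2 to 0.4 between domains.

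- Mean -0.5 SD, any low score makes the domain deficient: 16–21% have exactly two deficient domains. Severe is about 26–31% as printed, against about 9–12% under the graded rule.
- Mean -0.5 SD, domain means used instead: 7–9% have exactly two, and severe as printed falls to 11–14%.
- Mean -1.0 SD, any low score: a repeat run with 200,000 patients per setting gave 23–31% with exactly two. The 4–21% range therefore belongs to the one-score model and is not an upper limit.

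**Step 5: attention.** The classification sentence names a speed measure. The article describes TMT-A as a timed task that covers psychomotor speed, and Table 2 places it under attention. Digit span forward is in the same row of Table 2, but the article describes it as a measure of memory span and attention. The text does not settle whether a low digit span forward counts as an attention deficit.

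**The case against.** Several stronger readings are tempting, and the documents do not support them.

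- *No prevalence can be computed.* This goes too far. On the sensible reading, the unimpaired, mild and total impaired shares are determinate. Only the moderate/severe split is open.
- *The unimpaired rule needs only one adequate score.* The wording "Unimpaired: performance better than 1.5 standard deviations (SD) below the norm sample in any test considered for the classification" permits this literally. The mild class, defined by a deficit in a single domain, shows that every test is meant. This is a copy-edit and changes no estimate that anyone would report.
- *Nothing in the battery measures the attention criterion.* TMT-A is the evident speed measure. Only the role of digit span forward is unsettled.
- *The algorithm the study applies is defective.* The rule is taken from a cited study that is not among the documents, and a qualifier may have been lost in paraphrase. The printed text is wrong as it stands, but that does not show that the rule in use is wrong.

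Two further objections carry weight. The primary outcome is cognitive performance over time, analysed on composite and domain scores, and neither that analysis nor the follow-up sample size uses the classes. Which class counts as which diagnosis is also detail that an article may leave to the full protocol or analysis plan. The overlap differs from such an omission, because the article states the rule and the rule contradicts itself.

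**Conclusion.** The overlap is certain from the printed text: 24 of 81 domain patterns fall in both the moderate and the severe class, and nothing elsewhere in the article resolves it. Its consequence is limited to the moderate/severe split within the prevalence estimates.

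The size is only indicative. It depends on assumed patient means, correlations and domain scoring. The direction is the same in every scenario: the printed severe class is larger than under either alternative reading, in most scenarios by a factor of two or more. Because the primary repeated-measures analysis is untouched and the remedy is wording, this is a should-fix.

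**What to change.** Reconcile the printed definitions with the cited algorithm before any prevalence is reported, and make the classes exclusive and exhaustive. One version that does so:

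- Unimpaired: better than -1.5 SD in all classified tests.
- Mild: a deficit from 1.50 to below 2.0 SD in exactly one domain. This also closes the small gap between 1.99 and 2.0.
- Moderate: one deficit at or below -2.0 SD, or deficits in two or more domains that do not meet severe.
- Severe: deficits at or below -2.0 SD in at least two domains.

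Applied to the 81 patterns, this gives 1 unimpaired, 4 mild, 43 moderate and 33 severe (6 × 4 + 4 × 2 + 1 = 33), with no overlap. It does more than break the tie. The 16 + 5 = 21 patterns with three or four deficient domains but fewer than two severe deficits move from severe to moderate. The cited algorithm should therefore be consulted first, and this version is an example only.

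State as well whether digit span forward counts beside TMT-A in the attention domain.

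The cost is a wording change. Scores already collected are reclassified by program, and no new data are needed.

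### The impairment rule counts one low score out of nine as impairment, so the reported prevalence contains a sizeable base rate expected in cognitively normal people

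*Protocol article*

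**What the plan says.** All references are to the protocol article.

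- **Unimpaired** (The cognitive test battery): "performance better than 1.5 standard deviations (SD) below the norm sample in any test considered for the classification".
- **Impaired classes** (same section): these are counted by domain. Mild is "mild deficits (scores 1.50 to 1.99 SD below the norm sample) in only one domain". Moderate is a deficit in two domains or "a severe deficit (2.0 SD below the norm Sample) in one domain". Severe is deficits in at least two domains.
- **Scores that enter** (same section): "executive functions (semantic and phonemic fluency, working memory, and mental flexibility), verbal memory (immediate and delayed recall, recognition), visual memory (delayed recall"), together with symbol processing speed for attention. That is four executive scores, three for verbal memory, one for visual memory and one for attention. Table 2 lists two attention tests.
- **Scale** (same section): scores are norm-based z-scores adjusted for age and, where available, sex and education.
- **Use** (Statistical analysis): "We will investigate the proportion (percentage) of individuals that fulfill the above mentioned criteria at each given time point". These proportions serve as the prevalence estimates for mild and major impairment. The design is within-group.
- **Profile goal** (Introduction): the study asks "if a certain cognitive domain is more affected than others". No method is attached to this goal.
- **Continuous analysis** (Statistical analysis): a composite and one outcome per domain are the dependent variables in the repeated-measures ANOVA.

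**The concern.** A norm-referenced score falls at or below -1.5 SD in a known share of healthy people. When a person must clear that line on every one of nine scores, the chance of failing at least once is several times the single-score rate. Nothing in the rule allows for this, and there is no healthy comparison group in which the rate could be seen. A reader would take the reported percentage as disease-related impairment, although part of it comes from the scoring rule. This bears on goal (a), the extent of impairment.

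The unequal counts raise a second issue for goal (c). A domain with three or four scores has more chances to be flagged than a domain with one. If the profile were read from the percentage flagged in each domain, the multi-score domains would look more affected with no true difference. For executive function, the distortion would run in the direction that the Introduction already expects from earlier work in end-stage renal disease.

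**Working it through.** The document gives no expected rate of impairment in healthy people, so there is no figure of its own to reproduce here.

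**Reading of the rule.** Taken literally as at least one test, the word any in the unimpaired definition would make almost everyone unimpaired. The sensible reading is every test. The other classes are counted by domain. If a domain were judged on its mean, a person with one low score and an acceptable domain mean would fall into no class. The reading that leaves no gap is that one low score makes its domain deficient.

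**Inputs.** Cut-offs -1.5 and -2.0 SD, and domain sizes 4, 3, 1, 1 (sensitivity case 4, 3, 1, 2), come from the document. Joint normality and the correlations are assumptions.

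**Single score.** Φ(-1.5) = 0.0668 and Φ(-2.0) = 0.0228.

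**Independent scores.** P(at least one low of k) = 1 - (1 - 0.0668)^k:
- k = 3: 1 - 0.9332³ = 18.7%
- k = 4: 1 - 0.9332⁴ = 24.2%
- k = 9: 1 - 0.9332⁹ = 46.3%

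**One common correlation r.** P = 1 - E[{1 - Φ((-1.5 - √r·U)/√(1 - r))}^k], with U standard normal. For k = 9 this gives 39.1% at r = 0.2, 35.7% at 0.3, 32.3% at 0.4, 29.0% at 0.5, 25.6% at 0.6, 22.2% at 0.7 and 18.5% at 0.8.

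**Higher correlation within than between domains.** Score = √b·G + √(w - b)·D + √(1 - w)·e, where G is a person factor, D a domain factor, w the within-domain and b the between-domain correlation. One million simulated normal people, nine scores:

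| w / b | Any impairment | Executive | Verbal memory | Visual memory; attention | Moderate or worse |
|---|---|---|---|---|---|
| 0 / 0 | 46.3% | 24.2% | 18.7% | 6.7% | 22.4% |
| 0.3 / 0.2 | 38.2% | 21.0% | 16.9% | 6.7% | 19.9% |
| 0.4 / 0.3 | 34.8% | 19.9% | 16.3% | 6.7% | 18.6% |
| 0.5 / 0.3 | 33.7% | 18.5% | 15.3% | 6.7% | 17.7% |
| 0.6 / 0.4 | 30.2% | 17.0% | 14.3% | 6.7% | 16.3% |
| 0.7 / 0.5 | 26.8% | 15.4% | 13.3% | 6.7% | 14.7% |

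Moderate or worse means two or more low domains, or any score at or below -2.0 SD. The moderate and severe definitions both cover deficits in two domains, so that split was not computed.

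**Two attention scores (Table 2).** Any impairment becomes 40.8% at 0.3/0.2, 35.7% at 0.5/0.3 and 32.0% at 0.6/0.4. Attention alone becomes 11-12% over these cases.

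**Against sampling error.** With the 100 patients in the Abstract, the 95% half-width at 33% is 1.96·√(0.33·0.67/100) = 9.2 points. The base rate is well above that.

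**Domain contrast.** From 0.3/0.2 to 0.6/0.4, executive is 17.0/6.7 = 2.5 to 21.0/6.7 = 3.1 times a single-score domain. It exceeds verbal memory by only 17.0 - 14.3 = 2.7 to 21.0 - 16.9 = 4.1 points. The standard error of 18.5% with 100 patients is √(0.185·0.815/100) = 3.9 points.

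**The case against.** **The domain rule is inferred.** No sentence says that one low score makes a domain deficient, and the article relies on a published algorithm that is not shown. This stands as a caveat, and the result is conditional on the any-score reading. But the unimpaired definition is in the article itself, and only that reading leaves every person with a class.

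**The correlations are unknown.** Three scores come from one verbal memory test and two from one fluency test, so high within-domain correlation is plausible. This stands too. A flat statement that a third of healthy people would be called impaired is not supported; only the conditional range is. Even at r = 0.8 throughout, though, 18.5% is nearly three times 6.7%.

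**The profile may never use percent impaired.** A reader might infer that executive function will look worst by construction. The documents do not support that. The classification is tied only to person-level prevalence, domain outcomes enter the ANOVA as dependent variables, and the secondary outcome speaks of a profile of function, not a tally of impaired domains. The excess over verbal memory is also small enough for true deficits or chance to reverse it. What remains is that goal (c) asks for a comparison between domains, while the ANOVA is described for change over time and predictors, so its basis is open.

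**Norm adjustment and precedent.** Norming fixes the rate of each single score, not of the worst of several. Earlier use of the algorithm is a good reason to keep it, but does not remove the base rate.

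**Conclusion.** The point holds for prevalence. Under the any-score reading, and assuming normal scores with within/between-domain correlations of 0.3/0.2 to 0.6/0.4, about 30-38% of cognitively normal people would be classed at least mildly impaired and about 16-20% moderately or worse. Across all correlations tried, the first figure runs from 18.5% to 46.3%. Without a control group, the raw percentage cannot be read as impairment attributable to kidney disease or transplantation.

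For the profile, the point is conditional. If percent impaired were used, multi-score domains would look more affected than single-score ones, while executive function and verbal memory would differ little.

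A reader might also infer that the primary outcome is biased. It is not: a constant base rate does not by itself create a change before to after transplantation, and the continuous domain analyses do not use this rule.

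**What to change.** 1. **Prevalence.** Keep the adopted algorithm. Beside each prevalence, report the proportion expected in a normal population under the same rule and number of scores, by Monte Carlo over a stated range of correlations, taken from norm data where available. Correlations observed in patients need not match those in healthy people. Interpret prevalence as the excess over the expected rate. State in the text that unimpaired requires every score to be above the cut-off, and whether attention contributes one score or two.
2. **Profile.** State that goal (c) is compared on one norm-referenced score per domain with confidence intervals, not on percent impaired under the any-score rule. Put the domain scores on an equal scale using the norm SD, not the patients' own. A plain mean of four scores correlated at 0.5 has SD √((1 + 3·0.5)/4) = 0.79, so its low rate would be Φ(-1.5/0.79), about 2.9%, not 6.7%.
3. **Sensitivity analysis (optional).** Apply the -1.5 and -2.0 cut-offs to the domain scores. Every domain then has a 6.7% base rate, but about 19-21% of normal people would still have at least one low domain (18.8% at 0.6/0.4 and 20.1% at 0.5/0.3), and this should be said.

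**Cost.** No new data and a modest amount of analysis. The headline prevalence will read as less striking, and the expected rate depends on assumed correlations. Joint norm correlations across separately normed tests may not exist, in which case the range must be shown.
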